## Abstract

**Background:**

After the birth of a child, many mothers and fathers experience postpartum mental disorders like depression, anxiety, obsessive-compulsive disorder, stress or other illnesses. This endangers the establishment of a secure attachment between the children and their primary caregivers. Early problems in parent-child interaction can have adverse long-term effects on the family and the child’s well-being. In order to prevent a transgenerational transmission of mental disorders, it is necessary to evaluate psychotherapeutic interventions that target psychologically burdened parents of infants or toddlers. The aim of this trial is to investigate the efficacy of Parent-Infant-Psychotherapy (PIP) for mothers with postpartum mental disorder and their infants (0–12 months).

**Methods/design:**

In this open, randomized controlled intervention trial 180 mother-infant-dyads will be included and randomly allocated to 12 sessions of PIP or care as usual. The interventions take place either in inpatient adult psychiatric departments or in outpatient settings with home visits. The primary outcome is the change in maternal sensitivity assessed by the Sensitivity subscale of the Emotional Availability Scale (EAS) through videotaped dyadic play-interactions after 6 weeks. Secondary outcomes are maternal psychopathology, stress, parental reflective functioning, infant development and attachment after 6 weeks and 12 months. In addition, maternal attachment (AAI) and reflective functioning (AAI) will be analyzed as potential moderators, and resource usage in the German health system as well as associated costs will be evaluated.

**Discussion:**

There is increasing demand for well-controlled studies on psychotherapeutic interventions in the postpartum period that do not only focus on particular risk groups. This randomized controlled trial (RCT) represents one of the first studies to investigate the efficacy of PIP in inpatient psychiatric departments and outpatient care centers in Germany. The results will fill knowledge gaps on the factors contributing to symptom reduction in postpartum mental disorders and improvements in mother-child relationships and help in developing preventive and therapeutic strategies for the fragmented German health care system.

**Trial registration:**

German Register for Clinical Trials, ID: DRKS00016353.

## Background

Parental mental health problems during infancy are known to impact children’s emotional well-being and to modulate future developmental trajectories [1–3]. Postpartum mental health problems show high prevalence rates. In the first year after the birth of a child up to 22% of all mothers develop a postpartum depression (PPD) [4], and nearly 21% of all women suffer from postpartum anxiety [1] or obsessive-compulsive illnesses [5] with a high comorbidity of these disorders [6]. Parental mental health problems have been identified as major factors for problems in parent-child interaction and as risk factors for the child’s well-being [7, 8]. In contrast, a positive mother-child relationship is an essential resilience factor for child development. Maternal sensitivity towards the infant is seen as a key variable in mother-child interaction and secure attachment development [9–11]. The lack of sensitivity and the low level of parental skills associated with PPD are known to affect the interaction with the child which has adverse effects on the child’s development [12]. According to Lyons-Ruth [2], these malignant patterns increase the risk of disorganized attachment patterns and produce child psychopathologies [13]. Recent reviews emphasize that this relationship might be more complex and dependent on the severity of the problems and the presence of additional risk factors [14]. The available evidence thus favors interventions that focus on altering maternal or paternal sensitivity which in turn are more effective in enhancing attachment security [1, 4, 14].

Parent-Infant-Psychotherapy (PIP) has been developed as an intervention that aims to improve the attachment relationship between an infant and their parents to pave the way for a healthy child development [1, 15, 16]. PIP aims not only to reduce parental postpartum psychopathological symptoms but also to establish stable relationship patterns and to improve maternal or paternal sensitivity [15, 17, 18]. In comparison to other interventions, such as parenting programs, family support and medication [19–21], PIP shows high effect sizes on attachment development [15, 22]. Barlow et al. (see [15, 22]) recently reviewed eight clinical trials comprising either comparisons of PIP with no-treatment controls or other types of control groups. There was no difference in the efficacy of improving maternal sensitivity between all types of interventions, but PIP was significantly more effective in improving attachment security. While the meta-analysis of Barlow et al. did not reveal differences for measures of parental sensitivity [1], the authors clearly noted that the quality of the included studies was low while heterogeneity of these samples was high. The available evidence seems to indicate that PIP is more effective in subgroups of at-risk populations but more research addressing these limitations is needed [1, 23, 24].

This seems to be particularly true in case of mothers with mental health problems and young infants. Only four randomized controlled trials (RCTs) examining PIP with infants under 1 year of age have been published [1, 25–27]. These studies clearly differed in the addressed subpopulations (imprisoned mothers [25], depressed mothers [28], mothers experiencing social adversity [1], diverse maternal concerns and problems [26]) and the investigated settings (prison [25], outpatient setting [26], clinical setting [1] and home visits [28]). Only the RCT of Cooper et al. [28] required that study participants have a diagnosis of PPD as an inclusion criteria, while in the other studies participants had not to fulfill specific diagnoses at the time of recruitment [25, 26] or only research-related cut-offs for mental health problems [1]. Only one of these four studies [26] found evidence for an improvement of maternal sensitivity at post-intervention measurements and none revealed effects on infants’ attachment. Thus, there is currently neither evidence for the effectiveness of PIP with infants under 1 year of age nor conclusive evidence regarding clinical settings and psychiatric diagnoses. It therefore remains unclear whether this is due to the subpopulations examined, or the diagnostic criteria applied or the setting.

Thus, despite the clear benefits of attachment- and sensitivity-related interventions for the mother-child-dyad [19], a corresponding study of PIP with validation in inpatient psychiatric departments is still needed. Moreover, recent developments in child psychiatry provide evidence for the effectiveness of home treatment or home-based interventions [29–31]. Home visits by psychotherapists have the advantage of an intervention in the patient’s own environments, which might be particularly helpful for mothers in the postpartum period. It is assumed that staying in one’s own environment, and with the familiar daily routine, may have a positive influence on the treatment outcome. PIP home-based interventions have demonstrated to effectively improve the children’s attachment organization [32], but null effects on attachment measures and maternal sensitivity have also been reported [33, 34]. Again, there are large methodological differences between these studies.

In summary, previous randomized trials investigated the positive effect of PIP on the attachment quality of infants (and long-term effects up to preschool age [35]). In contrast to the present study, most of these studies have focused exclusively on specific risk groups or have taken place in outpatient settings and home visits but with relatively low diagnostic cut-offs [1, 25, 26, 28, 34]. The efficacy of PIP in inpatient departments and home-based interventions for mothers with diagnosed postpartum mental disorder will be investigated in this randomized controlled efficacy study.

## Methods/design

### Overview

The Parent-Infant-Psychotherapy in cohort- and intervention studies [Eltern-Säugling-KleinKInd-Psychotherapie mittels Prävalenz- und Interventionsstudien] (SKKIPPI) research project (www.skkippi.de) is a multicenter research project in Germany located in Berlin, Flensburg, Hamburg and Leipzig with the aim to examine epidemiology and treatment of psychosocial and mental disorders in the postpartum period. SKKIPPI is divided into an epidemiological cohort study that evaluates the prevalence of psychosocial and mental disorders in the postpartum period, the utilization of health and social care services, and their economic burden, and two randomized controlled intervention studies to evaluate the efficacy of PIP.

### Aims and hypotheses

The present RCT will be designed to evaluate the efficacy of focused PIP interventions in inpatient adult psychiatric departments with Mother and Baby Units (MBUs) or in outpatient psychiatric departments or via home visits. The decision about setting (inpatient or outpatient) will depend on the severity of the symptoms and/or maternal consent. It is hypothesized that in comparison to routine therapy (care as usual, CAU) mothers with mental disorders and their infants under 1 year of age will benefit from an increase in maternal sensitivity after 6 weeks of intervention. It will be expected that the routine therapy also reduces the psychopathological symptoms, but nevertheless has little or no effect on maternal sensitivity.

#### Secondary hypotheses

In comparison to routine therapy, PIP will be effective in reducing maternal psychopathological symptoms and psychological distress for mothers with mental disorders in the postpartum periodIn comparison to routine therapy, PIP will enhance parental reflective functioning in mothers with mental disorders in the postpartum periodIn comparison to routine therapy, PIP will enhance the rate of securely attached mother-child-dyads at 12 months’ follow-up

Subgroup analyses will be made between PIP and CAU depending on the setting (inpatient compared to outpatient/home visits). In addition, health economic analyses will be conducted for all groups (PIP as well as CAU). Therefore, the use of health and care services will be assessed, and associated costs will be estimated in order to systematically evaluate the economic burden of mothers with mental disorders in the postpartum period for the first time in Germany. Afterwards these cost results will be compared between the groups and will be related to the effectiveness results in order to get first hints on the interventions cost-effectiveness.

### Trial design

The study will be designed as a two-arm, open, multi-center RCT with parallel groups and blinded endpoint assessment (PROBE design; prospective, randomized, open, blinded endpoint) with 6 weeks of intervention.

Depending on the severity of the psychopathological symptoms and in agreement with the participants’ preferences, the decision for a particular treatment setting (inpatient or outpatient) will be made before randomization. After assignment to treatment setting, participants will be randomly allocated to either the PIP intervention group or the CAU control group. A biometrician will independently carry out a 1:1 block randomization with variable block length and stratification by setting (inpatient or outpatient) and study center. Treatment allocation is masked to the assigning personnel and there will be no special criteria for discontinuing or modifying the allocated intervention. Data of mothers and children will be assessed at three measurement points (see Fig. 1): at baseline after randomization and immediately before the intervention (T0), after the intervention at 6 weeks (T1) and at 12-month follow-ups (T2). Study centers are located in the German cities Berlin and Flensburg. At the time of writing additional effort is being made for a study center in Hamburg.

**Fig. 1 Fig1:**
[figure not shown]
Consolidated Standards of Reporting Trials (CONSORT) diagram describing the flow of the mother-child-dyads through the study. *PIP* Parent-Infant-Psychotherapy, *CAU* care as usual

### Participants

A sample of 180 mother-child-dyads is planned to participate in the study. After screening for eligibility, written informed consent and the decision about treatment setting, the participants will be randomly allocated to either the PIP intervention arm (planned *n* = 90) or the CAU control arm (planned *n* = 90; see Fig. 2). Mother-child-dyads will receive monetary compensation of €100 to take part in the study until the 12-month follow-up. To reduce attrition, trial participants will be thoroughly informed about study goals and assessment processes. During the time of participation, the study nurse will maintain contact with the participants and schedule follow-ups. Communication (e.g., for follow-up assessments) will either be conducted by e-mail or by telephone.

**Fig. 2 Fig2:**
[figure not shown]
Full Standard Protocol Items: Recommendations for Interventional Trials (SPIRIT) Figure. *EAS* Emotional Availability Scale, *M.I.N.I*. Mini International Neuropsychiatric Interview, *BSCL* Brief-Symptom-Checklist, *EPDS* Edinburgh Postnatal Depression Scale, *ASQ* Anxiety Screening Questionnaire, *IES-27* Scale for impulsive behavior and emotional dysregulation of Borderline Personality, *PRFQ*-1 Parental Reflective Functioning Questionnaire, *PSI* Parenting Stress Index, *AAI* Adult Attachment Interview, *SFS* German questionnaire Crying, Feeding, Sleeping, *CBCL* Child-Behavior-Checklist, *ET6–6-R* German development test, *SSP* Strange Situation Procedure

Inclusion criteria will be that the participants will be German-speaking mothers with an *International Classification of Diseases, version 10* (*ICD-10)* diagnosis of a mental disorder in the postpartum period and their infants under 1 year of age. Clinical screening for eligibility and diagnoses will be made by certified therapists, physicians or psychologists at the clinical study centers before inclusion in the study. Mothers can be referred either by health services, pediatricians, clinicians or other services, or by themselves.

Exclusion criteria will be a maternal *ICD-10* diagnosis of schizophrenia, substance abuse or recent suicidal ideation. Infants will be excluded when they show symptoms of alcohol embryopathy or severe chronic organic disease. Mothers and infants will be excluded when they are participants in further clinical trials or are undergoing another form of psychotherapy.

Participants will be recruited predominantly via health visiting services and mental health services, through links with community services, and advertisements in midwife practices, and pediatricians.

### Intervention

*Focused Parent-Infant-Psychotherapy* is a psychotherapeutic intervention in which mother-child-dyads are treated together. Individual sessions could also be held together with the father. PIP aims at fostering the parent-infant-relationship by supporting the parents’ ability to understand and mentalize the child’s affective states. It aims at promoting parental self-reflection and sensitivity to support the building and maintaining of parent-infant-relationships. PIP interventions are exclusively delivered by trained and supervised psychotherapists who are additionally certified in the PIP method. The manualized PIP ([name], [name], [name]: SKKIPPI-Studymanual for Parent-Infant-Toddler-Psychotherapy (PIP), unpublished) is a focused psychodynamic intervention with 12 succeeding sessions of approx. 50 min in 6 weeks (two sessions per week). The aims of PIP are clarification of problems, affect regulation, self-reflection, a change of perspective and the activation of the participants’ interpersonal resources. The intervention includes a mentalization-based approach, and works with reframing, an appropriate confrontation within a supportive framework, psychoeducation, the development of action strategies, and video-feedback. To enhance manual adherence, all study therapists will be additionally trained in the manual before the start of the treatment.

The inpatient treatment is characterized by interventions in adult psychiatric departments with MBUs or day hospitals. In inpatient settings, PIP will be provided in addition to standard therapeutic care. In outpatient settings PIP will be provided in the patients’ home environment or in psychiatric outpatient departments.

### Control

Participants in the CAU group will benefit from the standard (social) pedagogical and therapeutic care provided by the German health system over the intervention period of 6 weeks. Due to ethical considerations, no “waiting-list” group will be implemented. CAU, therefore, will resample a heterogeneous class of standard interventions. As a result, more intense and therapeutic care might be provided for mother-child-dyads in the inpatient settings compared to standard care in the outpatient setting. CAU in the inpatient setting could include counseling, body or occupational therapy and other psychiatric-therapeutic interventions for the participant. The frequency of these interventions will be generally lower than PIP treatment. CAU in outpatient setting could be other therapeutic interventions or (social) pedagogical care such as developmental psychological counseling or physiotherapy. Because this might result in heterogeneities in the number and intensity of CAU, all individual interventions will be documented.

### Assessment and outcome measures

#### Primary endpoint

*Maternal sensitivity*: the primary outcome of the current study will be maternal sensitivity at the end of 6-week intervention (T1) measured by the Emotional Availability Scale (EAS). EAS [36] is a widely used assessment for the quality of mother-child interaction with excellent psychometric properties. Fifteen-minute videotaped dyadic free-play interactions will be assessed at the mother’s home environment and will be coded by independent and reliable coders blind to treatment allocation. EAS will be assessed at all three measurement time-points and will be coded using a Likert Scale (1 to 7) on maternal sensitivity as well as three further maternal dimensions (structuring, non-intrusiveness and non-hostility) and two child dimensions (responsiveness to parent and involvement with parent).

#### Secondary endpoints

*Child attachment*: the most important secondary outcome will be child attachment measured by the Strange Situation Procedure (SSP) [37]. SSP is a standardized procedure of eight episodes to record the quality of the child’s attachment. The aim of SSP is to activate the child’s attachment system. The test will be conducted in the laboratory, recorded on video, and will be coded by reliable and independent coders blind to treatment allocation. This will result in the classification of the quality of infants’ attachment behavior as being secure (B), avoidant (A) or ambivalent (C). In addition, coders are also trained to classify disorganized (D) attachment qualities. Because SSP can only be validly assessed starting at an age of 11 months, it will only be measured at the 12-month follow-up time-point. Group differences in child attachment will be examined using binarized SSP classification (secure/ insecure).

Because no cut-off values are available, dichotomous response variables for the EAS sensitivity scale at T1 and T2 will be computed using the Reliable Change Index (RCI) as additional secondary endpoints (RCI > 1.96, see [38]).

Further secondary outcomes for the maternal psychopathological symptoms:
*M.I.N.I.* – The Mini International Neuropsychiatric Interview (M.I.N.I.) [39] is a structured diagnostic interview which assesses 20 psychiatric disorders by the *Diagnostic and Statistical Manual of Mental Disorders, 4th edition* (*DSM-IV)* and *ICD-10* diagnosis. The M.I.N.I. is used to verify the clinical diagnoses and will be administered at the mother’s home environment by trained interviewers at T0 and T2*BSCL* – The Brief-Symptom-Checklist (BSCL) [40] is a validated questionnaire for assessing maternal psychopathological symptoms. The BSCL will be measured at T0 and T1*EPDS* – The Edinburgh Postnatal Depression Scale (EPDS) [41] is a standard screening instrument to measure maternal symptoms of postnatal depression. The EPDS will be assessed at all three measurement time-points. Dichotomous response variables will be computed according to the cut-offs reported in [41] (EPDS < 12)*ASQ* – Maternal symptoms of anxiety disorder will be measured by the Anxiety Screening Questionnaire (ASQ) [42]. The ASQ is a questionnaire which assesses all anxiety disorders diagnosed by *DSM-IV* and *ICD-10.* It will be measured at T0 and T1*IES-27* – For assessing Borderline Personality Disorder, the Scale for impulsive behavior and emotional dysregulation of Borderline Personality Disorder (IES-27) [43] is used. The IES is a screening instrument which measures typical behavioral and perceptual patterns of this disorder. The questionnaire will be assessed at T0 and T1*PRFQ-1* – The Parental Reflective Functioning Questionnaire (PRFQ) [44] is a validated questionnaire which measures the mother’s ability to mentalize in context of the relationship to her child. The questionnaire will be assessed at all three measure times. Because no cut-off values are available, dichotomous response variables for the PRFQ will be computed based on the RCI > 1.96 criterion [38]*PSI* – The German version of the Parenting Stress Index (PSI) [45, 46] is a questionnaire which measures the maternal stress at T0, T1 and T2. Because no cut-off values are available, dichotomous response variables for the PSI will be computed based on the RCI > 1.96 criterion [38]*AAI* – Maternal attachment style and reflective functioning, i.e., the capacity to mentalize, are considered as important moderators in the present design and are assessed using the Adult Attachment Interview (AAI) [37]. AAI is a semi-structured interview with excellent psychometric properties to evaluate the maternal “state of mind” with respect to attachment [37]. AAI will be conducted in the laboratory by trained interviewers at baseline (T0), transcribed, and subsequently scored by reliable and independent coders blind to treatment allocation

Secondary outcome measures for the child:
*SFS* – The infant’s symptoms are measured by using the German questionnaire Crying, Feeding, Sleeping (SFS) [47]. The SFS assesses problems in the child’s behavioral regulation and dysfunctional communication patterns, and stress symptoms of the primary caregivers. The questionnaire will be assessed at T0 and T1*CBCL* – To detect the child’s emotional and behavioral problems, the Child-Behavior-Checklist (CBCL) [48] is used. The CBCL is validated at a child’s age of 18 months and will, therefore, be assessed at 12-month follow-up only*ET-6-6-R* – The level of social-emotional, cognitive, motor and language development of the child is assessed by the German development test ET6–6-R [49]. The ET-6-6-R is a standardized test for children aged from 6 months to 6 years that measures the developmental status of the child. The test will be measured at the mother’s home environment at T1 and T2.

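### Given entry from birth to under 1 year, the ET6-6-R at T1 and the CBCL at T2 fall below their stated ages for 38.5% and 38.5–50% of the eligible age window

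*Protocol article*

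**What the plan says.** **Entry age.** The inclusion criteria in the Participants section admit mothers with a diagnosed postpartum disorder and "their infants under 1 year of age". The abstract gives the range as 0–12 months. Neither sets a lower age limit.

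**Visits.** The Trial design section places T0 "at baseline after randomization and immediately before the intervention (T0"), and the later visits "after the intervention at 6 weeks (T1) and at 12-month follow-ups (T2"). It does not say whether the 12 months run from T0 or from T1.

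**ET6-6-R.** The Secondary endpoints section calls it a "standardized test for children aged from 6 months to 6 years" and schedules it at the mother's "home environment at T1 and T2".

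**CBCL.** The same section says that it is validated at a child's "age of 18 months and will, therefore, be assessed at 12-month follow-up only".

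**Analysis.** The section on sample size and statistical analyses makes the Full Analysis Set, all randomised dyads, the default for every analysis. Analyses of the secondary outcomes carries the primary strategy over to the secondary outcomes. Neither section mentions an age restriction for these two instruments.

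**The concern.** The CBCL sentence draws a conclusion from an age requirement: the instrument needs a child of 18 months, so the 12-month visit is the right place for it. That works only for a child who was already about half a year old at entry. The ET6-6-R has the same problem in a plainer form, because its lower age limit is stated just before a schedule that includes a visit 6 weeks after baseline.

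The article handles this correctly elsewhere. The Strange Situation Procedure is said to be valid from 11 months and is held back to T2, when every child is at least 12 months old.

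What is at stake is the interpretation of two child outcomes. The abstract lists infant development after 6 weeks among the secondary outcomes, and the ET6-6-R is the only developmental test described at T1. The CBCL is measured at T2 alone, so no other visit can stand in for it. Followed as written, the schedule leads either to scores from children outside the stated age range or to missing values that nobody planned for.

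**Working it through.** The article gives no figure for the share of infants affected, so there is nothing to reproduce. The check is age arithmetic.

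**Inputs from the article**
- Entry age: 0 to under 12 months (Abstract; Participants).
- T1: 6 weeks after T0. T2: 12 months, origin not stated (Trial design).
- ET6-6-R minimum age: 6 months. CBCL age: 18 months, read here as a minimum (Secondary endpoints).
- Planned sample: 180 dyads (Participants).

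**Step 1. Convert 6 weeks to months.** Weeks per month = 365.25 / 12 / 7 = 4.348. Then 6 / 4.348 = 1.38 months.

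**Step 2. Age range at each visit.**
- T1: 0 + 1.38 to 12 + 1.38, about 1.4 to 13.4 months.
- T2 counted from T0: 12 to 24 months. Counted from T1: about 13.4 to 25.4 months.

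**Step 3. Entry-age cut-off = stated minimum age − time from T0 to the visit.**
- ET6-6-R at T1: 6 − 1.38 = 4.62 months.
- CBCL at T2, counted from T0: 18 − 12 = 6.0 months.
- CBCL at T2, counted from T1: 18 − 12 − 1.38 = 4.62 months.

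**Step 4. Share of the eligible window = cut-off / 12.**
- ET6-6-R at T1: 4.62 / 12 = 38.5%.
- CBCL at T2: 6.0 / 12 = 50%, or 4.62 / 12 = 38.5%.

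These are shares of the age window. They become shares of infants only if entry age is uniform, in which case about 69 of 180 (0.385 × 180 = 69.3) are too young for the ET6-6-R at T1, and 90 (or about 69) of 180 are too young for the CBCL at T2.

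**Step 5. Vary the entry-age distribution.** The article gives none, so the rows below are assumptions: Beta distributions scaled to 0–12 months, with the uniform for comparison.

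| Assumed entry age | Mean (months) | ET6-6-R at T1 too young | CBCL too young, T2 from T0 | CBCL too young, T2 from T1 |
|---|---|---|---|---|
| Beta(1.5, 3) | 4.0 | 62.9% | 78.4% | 62.9% |
| Beta(2, 3) | 4.8 | 49.9% | 68.8% | 49.9% |
| Uniform | 6.0 | 38.5% | 50.0% | 38.5% |
| Beta(2, 2) | 6.0 | 33.1% | 50.0% | 33.1% |
| Beta(3, 2) | 7.2 | 16.2% | 31.2% | 16.2% |
| Beta(3, 1.5) | 8.0 | 10.5% | 21.6% | 10.5% |

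Even the lowest value, 10.5%, is about 19 of 180 children (0.105 × 180 = 18.9).

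**Step 6. Instruments that pass the same check.** At T2 the youngest child is 12 months old. That is above the 6-month floor of the ET6-6-R and the 11-month floor of the Strange Situation Procedure, so neither has an age problem at T2.

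**The case against.** The best reply has four parts.

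*The share of infants is unknown.* This stands. A reader might infer from the arithmetic that 40–50% of the infants in the trial will be too young. The article does not support that: it gives no entry-age distribution, and recruitment could lean towards younger or older infants.

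*Nothing says that invalid scores will be pooled with valid ones.* A reader might infer such a plan from the schedule. The article does not state one, and per-instrument age rules may sit in the full protocol or the analysis plan. That stands as far as handling rules go. It does not excuse the text itself: the CBCL sentence draws a conclusion that is false for part of the eligible population, and the ET6-6-R schedule conflicts with the age limit given beside it. With all randomised dyads as the default analysis set, the written plan offers no way round.

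*The CBCL wording is loose.* Validated at 18 months may not mean a strict minimum, and the origin of the 12 months is open. Both are carried as stated assumptions. Reading it as exactly 18 months would widen the mismatch.

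*The consequences are limited.* This also stands. Age at entry is fixed before randomisation, so the problem does not by itself favour an arm. It costs precision and interpretability. The article declares the analyses of secondary outcomes exploratory, and none of its three listed secondary hypotheses concerns the ET6-6-R or the CBCL.

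**Conclusion.** The inconsistency is real and follows from the article's own figures. For the ET6-6-R at T1, 38.5% of the eligible entry-age window is below the stated minimum. For the CBCL at T2 it is 50% of the window if T2 is counted from T0, or 38.5% if counted from T1, provided that 18 months is a minimum age. The claim that the 12-month visit settles the CBCL age requirement is wrong for the youngest entrants.

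The share of enrolled children cannot be fixed from the document. Under the assumed distributions it runs from roughly 63% down to 11% for the ET6-6-R, and from 78% down to 11% for the CBCL across both readings of T2.

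This should be corrected, but it does not threaten the trial's main conclusion. The primary endpoint, the sample size, the Strange Situation Procedure and the ET6-6-R at T2 are unaffected.

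**What to change.** 1. Reconcile the entry age (Participants), the visit timing (Trial design) and the instrument ages (Secondary endpoints). State whether T2 is counted from T0 or T1, and whether 18 months is a minimum for the CBCL.
2. Make T2 the main time-point for the ET6-6-R, since every child is then at least 12 months old.
3. Restrict the ET6-6-R analysis at T1 and the CBCL analysis at T2 to infants whose age at randomisation plus the scheduled visit interval reaches the instrument's stated minimum. Use the scheduled interval: actual age at the visit or at completion depends on timing after randomisation, which could differ by arm. Defined this way, the subset is fixed before treatment and the randomised comparison within it is kept.
4. Adjust these analyses for child age at randomisation.

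The cost is wording in the schedule and analysis sections, and fewer children in the two restricted analyses. Under a uniform entry age, about 69 of 180 would drop out of the ET6-6-R analysis at T1, and 69 to 90 out of the CBCL analysis, before any attrition.

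Sending the CBCL later, when a child reaches 18 months, would recover those children, but it should be optional only. A newborn entrant would complete it about 18 months after T0, whereas older entrants would do so at 12 months, so time since randomisation would vary with age.
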